#### Planned analysis

The primary analysis will evaluate the incidence density of *S. aureus* or *P. aeruginosa* ICU pneumonia; its calculation will depend on time from admission (for outcome ICU pneumonia) or time from ventilation (for outcome ventilator-associated pneumonia).

For the primary and secondary objectives, advanced survival techniques (competing risks and multistate models) will be applied. Discharge and death will be considered as competing events for ICU pneumonia. Adapted Cox regression models will be applied for each event separately as well as for the sub-distribution of ICU pneumonia. The clustering of the data (readmission, patients within ICU, country) will be acknowledged using shared frailty methodology, stratification or robust variance. The time-dependency of cumulative hazards and incidences will be graphically displayed, by risk factors of interest. Hazard ratios with 95% CI will be calculated univariately and selected for the multivariate model using an established Akaike’s information criterion for model selection. A risk prediction model will be developed to quantify the risk for acquiring *S. aureus* or *P. aeruginosa* ICU pneumonia during ICU stay by using a composite score of independent risk factors.

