## Methods

### Objectives

The primary objectives of this study are to determine the incidence of:
*S. aureus* ICU pneumonia through ICU stay; and
*P. aeruginosa* ICU pneumonia through ICU stay; andtheir independent associations with patient-related factors (e.g. colonization status, baseline serum antibody levels against *S. aureus* or *P. aeruginosa* antigens) and contextual factors.

The key secondary objectives are to develop risk prediction models to quantify the risk of acquiring (i) *S. aureus* or (ii) *P. aeruginosa* ICU pneumonia during ICU stay, by using a composite score of independent risk factors identified through primary objective 1 and 2. Other secondary and exploratory objectives can be found on ClinicalTrials.gov, under identifier NCT02413242, or in the online (Additional file 1: S.01).

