#### Study cohort population

Surveillance patients that meet the eligibility criteria described below for the study cohort population will be enrolled. 2000 study cohort subjects are required to meet the objectives of this study. Study cohort subjects are approached for informed consent based on their *S. aureus* colonization status at ICU admission. Subjects will be enrolled in a 1:1 ratio of *S. aureus* colonized subjects to non *S. aureus* colonized subjects with 1000 subjects in each stratum. A similar temporal distribution of enrolled *S. aureus* colonized and non *S. aureus* -colonized subjects will be managed by selecting the first non-colonized subject after including a colonized subject. For subjects unable to provide consent for any reason, a legally accepted representative may consent on the subject’s behalf at the time of enrollment.

Inclusion criteria for study cohortParticipant is 18 years or older at the time of enrollment.Participant is on mechanical ventilation at ICU admission, or is (expected to be) within 24 h thereafter, based on investigator’s judgment.Expected stay in ICU is 48 h or longer based on investigator’s judgment.
*S. aureus* colonization status is known within 72 h after start of first episode of mechanical ventilation and according to the result, the patient qualifies for enrollment.Written informed consent from subject / legally accepted representative within 72 h after start of first episode of mechanical ventilation.

Exclusion criteria for study cohortPrevious participation as a subject in the study cohort of this study.Simultaneous participation of the subject in any preventive experimental study into anti-staphylococcus or anti-pseudomonas aeruginosa interventions.Expected death (moribund status) within 48 h, or ICU discharge of the participant within 24 h, at the moment of informed consent.

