### Statistical analysis

#### Sample size calculation

Sample size calculations are based on the expected incidence precision of *S. aureus* ICU pneumonia and *P. aeruginosa* ICU pneumonia, since the primary objective of the study is to identify the patient groups most at risk for this outcome.

Assuming an incidence of *S. aureus* ICU pneumonia of 12.5% and 1.5% in the *S. aureus* colonized group and non *S. aureus* colonized group respectively, this would result in an overall incidence of 7% within the 2000 study cohort subjects, or 140 *S. aureus* ICU pneumonia endpoints [9]. The overall incidence estimate would have precision of 1.12% (95% confidence interval [CI]: 5.9%–8.12%, using normal approximation).

For *P. aeruginosa* ICU pneumonia, the overall incidence is estimated regardless of colonization status at ICU admission. Assuming an overall incidence of *P. aeruginosa* ICU pneumonia of 2.5% within the 2000 study cohort subjects, this would result in 50 *P. aeruginosa* ICU pneumonia endpoints. The overall incidence estimate would have precision of 0.68% (95% CI 1.82%–3.18%, using normal approximation).

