### Enrichment strategy

In this study, 50% of the study cohort population is *S. aureus* colonized at ICU admission to ‘enrich’ the study population with *S. aureus* carriers (in nose or lower respiratory tract), while this naturally occurs in approximately 20–25% of the ICU population [10]. This was chosen as *S. aureus* carriage is being studied as one of the main known risk factors for subsequent *S. aureus* disease, thus without enrichment, the population needed for equal precision would be much larger [9, 11, 12]. However, the limitation of this choice is that one can argue that a population as such is not representative of the general ICU population, thus incidence estimation as well as assessing risk factors for *P. aeruginosa* ICU pneumonia may be suboptimal. We acknowledge this, and for this reason the surveillance population was included. Their data will allow distribution of baseline factors with the study cohort in an effort to assess the ubiquity of results across both groups. Furthermore, it can serve to identify potential bias between participants and non-participants. Considering that *P. aeruginosa* colonization at ICU admission is relatively rare and that colonization often occurs after ICU admission, no recruitment selection for *P. aeruginosa* colonized subjects will take place [13].

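### AIC selection, read literally from unadjusted hazard ratios, decides whether exposures named in the primary objective get an adjusted estimate, and carriage could mask a protective S. aureus antibody effect

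*Protocol article*

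**What the plan says.** - Protocol article, Objectives: beside the two incidences, the primary objectives cover "independent associations with patient-related factors (e.g. colonization status, baseline serum antibody levels against" antigens of either pathogen, and contextual factors.
- Planned analysis: "Hazard ratios with 95% CI will be calculated univariately and selected for the multivariate model using an established" Akaike "information criterion for model selection". The sentence exempts no exposure.
- Study cohort population: enrolment is 1:1 by S. aureus colonization, "with 1000 subjects in each stratum".
- Sample size calculation: the assumed incidences are "ICU pneumonia of 12.5% and 1.5% in the" colonized and non-colonized groups.
- Enrichment strategy: S. aureus "carriage is being studied as one of the main known risk factors for subsequent" disease by that organism.

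**The concern.** An independent association is an adjusted one. Under the stated rule, an exposure that is not selected has only an unadjusted HR, so the primary question about it is not answered.

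The design makes this more than a formality. Half the cohort carries a factor with an assumed 12.5 / 1.5 = 8.3-fold risk. The unadjusted HR of anything correlated with carriage is therefore confounded by it. A protective factor that is commoner in carriers moves towards the null and may be screened out before carriage is adjusted for.

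At stake is the antibody result. The article says the study is meant to inform later trials of monoclonal antibodies and to identify who may benefit most. The risk score is to be built from the independent risk factors, so a dropped antibody term could be missing there too.

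**Working it through.** **1. The plan's own figures.** Overall S. aureus incidence is 0.5 × 12.5% + 0.5 × 1.5% = 7%, or 140 events in 2000. The half-width is 1.96 × √(0.07 × 0.93 / 2000) = 1.118%, which matches the stated 1.12%. For P. aeruginosa, 2.5% gives 50 events and a half-width of 0.684%, which matches 0.68%. The carriage HR implied by the two risks is ln(0.875) / ln(0.985) = 8.8.

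**2. The selection threshold.** For one parameter, AIC keeps a term when the likelihood-ratio statistic exceeds 2, that is |z| > 1.414 or p below about 0.157.

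**3. Assumptions not in the documents.** Antibody is normal with SD 1 within each carriage stratum. Its mean is higher in carriers by δ SD. The true log HR per SD is β. Follow-up is fixed and there are no competing events.

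**4. Size of the confounding.** Of the 140 expected cases, 125 are carriers and 15 are non-carriers. The mean antibody in cases, relative to the cohort mean, is about β + (δ/2) × (125 − 15)/140 = β + 0.393δ. The cohort variance is 1 + δ²/4. So, approximately:

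unadjusted log HR ≈ (β + 0.393δ) / (1 + δ²/4), with SE ≈ 1/√[140 × (1 + δ²/4)].

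Example with HR 0.7 and δ = 0.5: (−0.357 + 0.196) / 1.0625 = −0.151, so the unadjusted HR is 0.86. The SE is 0.082 and z = −1.84. The chance that |z| stays below 1.414 is about 33%.

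| True HR per SD | Shift δ | Unadjusted HR | Dropped by univariable AIC, approximation | Dropped, simulation |
|---|---|---|---|---|
| 0.7 | 0.3 | 0.79 | 8% | 7–11% |
| 0.7 | 0.5 | 0.86 | 33% | 31–35% |
| 0.7 | 0.8 | 0.96 | 80% | 80–84% |
| 0.8 | 0.3 | 0.90 | 57% | 52–59% |
| 0.8 | 0.5 | 0.98 | 82% | 78–83% |
| 0.8 | 0.8 | 1.08 | 65% | 62–70% |

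The simulation column is the range over repeated simulations of the plan's design (300 to 600 cohorts per setting where the number is recorded). The rate falls again in the last row because the unadjusted HR has crossed 1: antibody is then kept more often, but its unadjusted HR points the wrong way.

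**5. With carriage already in the model.** The SE is about 1/√140 = 0.0845. At HR 0.7, z = −4.22 and AIC drops antibody in 0.3% of studies. At HR 0.8, z = −2.64 and it drops antibody in 11%. Simulation gave 0–1% and 6–12%, whatever the shift.

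**6. Where masking disappears.** At δ = 0 the approximation for the univariable screen gives the same 0.3% and 11%, so nothing is lost to masking. At δ = −0.3 or −0.5, simulated drop rates were 0% (HR 0.7) and at most 0.2% (HR 0.8). At HR 0.7 the rate was still only 1% at a shift of 0.1 and 4% at 0.2.

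**7. A different antibody scale.** With antibody as high or low, a true HR of 0.6, and high levels in 60% of carriers and 40% of non-carriers, the unadjusted HR was about 0.85. The univariable screen dropped it in 66% of 500 simulated studies, against 6% with carriage in the model.

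**8. P. aeruginosa, no masking assumed.** With 50 events the SE is about 1/√50 = 0.141 per SD. AIC would delete a true HR of 0.8 (z = −1.58) in about 43% of studies and 0.7 (z = −2.52) in about 13%.

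**The case against.** The strongest reply is that the sentence is ambiguous. AIC ranks models, so the text may mean that univariable HRs are reported and AIC then chooses among multivariable models. This largely stands: on that reading masking is mostly removed and the S. aureus drop rates fall to those in step 5. What remains is that AIC may still delete an exposure named in the primary objective, and steps 5 and 8 show how often.

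A second reply is that forced-in terms are a detail for the full protocol or analysis plan, and this is a condensed article. Silence alone would indeed be no finding. Here, however, the article states a selection rule, and followed as written that rule can leave a primary question without an adjusted estimate.

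Third, no passage says that antibody is higher in carriers, and the antibody effect is also assumed. This stands in full. The percentages show what the rule can do, not how it is expected to perform.

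Three stronger readings are tempting but unsupported:
- That all named exposures are at risk. Carriage, at 12.5% against 1.5%, would pass any screen for S. aureus pneumonia.
- That the masking extends to P. aeruginosa pneumonia. Nothing in the documents makes S. aureus carriage a strong risk factor for that outcome. Only the general deletion risk applies there.
- That the antibody question will go unanswered. That would need both the literal reading and a material positive link between antibody and carriage.

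Antibody is also listed as an example among patient-related factors, and the plan would still show its univariable HR and possibly cumulative incidence curves. Those are unadjusted and do not answer the question of independent association.

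**Conclusion.** The point holds in a conditional form. The objectives ask for independent associations with named exposures, while the analysis text lets data-driven selection decide whether those exposures are estimated with adjustment.

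On the literal reading, and if S. aureus antibody is 0.3 to 0.8 SD higher in carriers with a true HR of 0.7 to 0.8 per SD, a univariable AIC screen drops it in roughly 8% to 84% of studies. With carriage in the model the figure is about 0% to 12%, so the same data would usually have shown the effect. With no association or the reverse one there is no masking. If AIC acts only among multivariable models, what is left is occasional deletion of a named exposure, more often with the 50 P. aeruginosa events.

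The change is worth making because it is nearly free and removes the dependence on an unknown correlation.

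**What to change.** State in Planned analysis that:
- S. aureus carriage (the sampling stratum) and the baseline antibody against S. aureus are kept in the S. aureus pneumonia models.
- The P. aeruginosa colonization status and antibody are kept in the P. aeruginosa models.
- Their adjusted HRs with 95% CI are reported whatever AIC shows.
- AIC is applied only to the other candidates, with these terms already in the model and not on unadjusted HRs.

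This also settles which way the selection sentence is to be read. It needs a sentence or two of wording and no new data. One or two degrees of freedom are always spent in each model, which is noticeable mainly with about 50 P. aeruginosa events.

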### Quality assurance

Data will be entered in a web-based electronic data capture system that was designed for **ASPIRE-ICU.** The study site will enter data in the electronic data capture system from the subject’s source documents (i.e. medical chart). Information linking the subject ID to the subject’s medical file (only applicable for study cohort subjects) will be kept in a secure place at the participating study site.

Monitoring will include 100% source data verification for the first three enrolled study cohort subjects at each site, and then 10% of the remaining enrolled study cohort subjects.

## Discussion

This manuscript describes the objectives and design of **ASPIRE-ICU**, an observational cohort study addressing risk factors for *S. aureus* and *P. aeruginosa* ICU pneumonia. Certain choices have been made in the design that warrant mention and further discussion.

### Definition of pathogen-specific pneumonia

The definition of *S. aureus* or *P. aeruginosa* ICU pneumonia is based on pre-defined pneumonia criteria in combination with the presence of the bacterium in an appropriate sample around the time of diagnosis, which are aligned with endpoints being used for two randomized controlled trials for prevention of *S. aureus* and *P. aeruginosa* pneumonia [8]. Thus, in case of cultures that yield multiple possible pathogens, it may be that the diagnosis of *S. aureus* or *P. aeruginosa* pneumonia is made incorrectly. The distinction between colonization and infection is sometimes difficult to assess. There is however no ‘reference standard’ to reliably assess the causative pathogen [3]. We have contemplated quantitative cultures in all pneumonia patients, but it was not feasible to implement this at each site. Quantitative measurements will however be applied on study samples received by the central laboratory, and thus will provide additional retrospective information. Furthermore, other outcomes, such as mortality will provide objective outcome information in addition to a diagnosis of pneumonia.

### Enrichment strategy

In this study, 50% of the study cohort population is *S. aureus* colonized at ICU admission to ‘enrich’ the study population with *S. aureus* carriers (in nose or lower respiratory tract), while this naturally occurs in approximately 20–25% of the ICU population [10]. This was chosen as *S. aureus* carriage is being studied as one of the main known risk factors for subsequent *S. aureus* disease, thus without enrichment, the population needed for equal precision would be much larger [9, 11, 12]. However, the limitation of this choice is that one can argue that a population as such is not representative of the general ICU population, thus incidence estimation as well as assessing risk factors for *P. aeruginosa* ICU pneumonia may be suboptimal. We acknowledge this, and for this reason the surveillance population was included. Their data will allow distribution of baseline factors with the study cohort in an effort to assess the ubiquity of results across both groups. Furthermore, it can serve to identify potential bias between participants and non-participants. Considering that *P. aeruginosa* colonization at ICU admission is relatively rare and that colonization often occurs after ICU admission, no recruitment selection for *P. aeruginosa* colonized subjects will take place [13].

### Routine surveillance

This study utilizes routine *S. aureus* screening conducted at each participating site as the basis for eligibility assessment. For consistency of screening results across sites, all swabs will be plated under protocol on the same chromogenic agar plates (Colorex agar, bioTRADING Benelux) provided by the ASPIRE-ICU study team. In the original protocol, a nose swab and ETA sample (sputum sample if non-intubated) are collected at screening. However, soon after study start, the protocol was amended to include a throat sample as a LRT sample, in case ETA and sputum were both not feasible.

### Future perspectives

In this era of increasing antimicrobial resistance, the research field is steadily exploring other therapies, for example prophylactic therapies such as antibody-based preventive measures. A potential advantage of monoclonal antibodies (mAbs) is that they will not encourage bacterial resistance to the same extent as antibiotics, and may even augment antibiotic effectiveness [14]. This study was designed in part to provide crucial information on the incidence, patient-related and contextual factors of ICU pneumonia caused by *S. aureus* and *P. aeruginosa*, but also inform the design of future phase III trials, that will investigate mAbs effectiveness against *S. aureus* and *P. aeruginosa*. Two large COMBACTE phase II trials, SAATELLITE (A Human Monoclonal Antibody Against *Staphylococcus aureus* Alpha Toxin in Mechanically Ventilated Adult Subjects) and EVADE (Effort to Prevent Nosocomial Pneumonia Caused by *Pseudomonas aeruginosa* in Mechanically Ventilated Subjects) have already started [8]. SAATELLITE investigates the effect of MEDI4893, a mAb targeting *S. aureus* alpha toxin and EVADE studies MEDI3902, which is another mAb that simultaneously targets PcrV and Psl on the surface of the *P. aeruginosa* bacterium, in subjects at risk for ICU pneumonia [5, 6, 8]. These targeted therapies, if proven effective, may be used in the future for patients at highest risk. This study will help to identify the subset of patients that will likely benefit most.

## Conclusion

This epidemiological cohort study on *S. aureus* and *P. aeruginosa* ICU pneumonia aims to add significant information to the literature on predictors for this event. This will help refine the design of Phase III trials and may benefit patients at risk for nosocomial infections, by providing protective measures.

## Abbreviations

ASPIRE-ICU: Advanced understanding of *Staphylococcus aureus* and Pseudomonas aeruginosa Infections in EuRopE
CI: Confidence interval
COMBACTE: COMBatting AntibiotiC resisTance in Europe
ETA: Endotracheal aspirate
ICU: Intensive Care Unit
LOS: Length of stay
LRT: Lower respiratory tract
mAb: Lower respiratory tract
*P. aeruginosa*: *Pseudomonas aeruginosa*
*S. aureus*: *Staphylococcus aureus*
